## Abstract

**Background:**

Chronic pain and early cognitive decline, which are costly to treat and highly prevalent among older adults, commonly co-occur, exacerbate one another over time, and can accelerate the development and progression of Alzheimer disease and related dementias. We developed the first mind-body activity program (Active Brains [AB]) tailored to the needs of older adults with chronic pain and early cognitive decline. Results from our previous study strongly supported the feasibility of conducting AB remotely and provided evidence for improvements in outcomes.

**Objective:**

We are conducting a single-blinded, National Institutes of Health stage-2, randomized clinical trial to establish the efficacy of AB versus a time-matched and dose-matched education control (Health Enhancement Program [HEP]) in improving self-reported and objective outcomes of physical, cognitive, and emotional functions in 260 participants. The methodology described in this paper was informed by the *lessons learned* from the first year of the trial.

**Methods:**

Participants are identified and recruited through multidisciplinary clinician–referred individuals (eg, pain psychologists and geriatricians), the Rally Research platform, social media, and community partnerships. Interested participants complete eligibility screening and electronic informed consent. Baseline assessments include self-report, performance-based measures (eg, 6-min walk test) and objective measures (eg, Repeatable Battery for the Assessment of Neuropsychological Status). Participants are mailed a wrist-worn ActiGraph device (ActiGraph LLC) to passively monitor objective function (eg, steps) during the week between the baseline assessment and the beginning of the programs, which they continue to wear throughout the programs. After baseline assessments, participants are randomized to either AB or HEP and complete 8 weekly, remote, group sessions with a Massachusetts General Hospital psychologist. The AB group receives a Fitbit (Fitbit Inc) to help reinforce increased activity. Assessments are repeated after the intervention and at the 6-month follow-up. Coprimary outcomes include multimodal physical function (self-report, performance based, and objective). Secondary outcomes are cognitive function (self-report and objective), emotional function, and pain.

**Results:**

We began recruitment in July 2022 and recruited 37 participants across 4 cohorts. Of them, all (n=37, 100%) have completed the baseline assessment, 26 (70%) have completed the posttest assessment, and 9 (24%) are actively enrolled in the intervention (total dropout: n=2, 5%). In the three cohorts (26/37, 70%) that have completed the AB or HEP, 26 (100%) participants completed all 8 group sessions (including minimal makeups), and watch adherence (1937/2072, 93.48%, average across ActiGraph and Fitbit devices) has been excellent. The fourth cohort is ongoing (9/37, 24%), and we plan to complete enrollment by March 2026.

**Conclusions:**

We aim to establish the efficacy of the AB program over a time-matched and dose-matched control in a live video-based trial and test the mechanisms through theoretically driven mediators and moderators. Findings will inform the development of a future multisite effectiveness-implementation trial.

**Trial Registration:**

ClinicalTrials.gov NCT05373745; https://classic.clinicaltrials.gov/ct2/show/NCT05373745

**International Registered Report Identifier (IRRID):**

DERR1-10.2196/47319

## Introduction

### Background

Chronic pain (CP; ie, pain lasting ≥3 mo) and early cognitive decline (ECD; ie, subjective cognitive decline [1] or mild cognitive impairment [2]) commonly co-occur among older adults. An estimated 60% to 75% of people aged >65 years report at least some persistent pain [3]. Older adults with CP are twice as likely to also report ECD [4,5]. The presence of both CP and ECD has an even greater negative impact on older adults’ physical and emotional functioning than either of these conditions separately [6]. Pain impairs cognitive function, accelerates ECD, and is a modifiable risk factor for developing Alzheimer disease and related dementias [5,7]. In contrast, ECD alters pain perception, reduces treatment compliance, and increases the risk for subsequent disability [8]. Consequently, older adults with CP along with ECD (CP-ECD) can become caught in a *disability spiral* whereby cognitive, physical, emotional, and social functioning are interrelated and progressively worsen over time [9,10]. Addressing this comorbidity in the ECD stage is an unexplored opportunity to stop the disability spiral and potentially slow the transition toward dementia.

The current model of treating the CP-ECD comorbidity is incomplete [11]. Medications have limited efficacy [11-15], increase the risk of adverse events such as falls [16], and have harmful side effects that can impair cognition [17]. Walking interventions provide a safe, nonpharmacological alternative for older adults [18,19], with benefits for both CP and ECD [20-22]. However, older adults with CP-ECD face numerous barriers to walking, including pain misconceptions (eg, *hurt equals harm*), maladaptive thoughts (eg, fear avoidance and pain catastrophizing), and rigid regimens (eg, interferes with life and very difficult to implement) [23-26]. Mind-body interventions can directly address these barriers to sustained walking by teaching evidence-based skills (eg, diaphragmatic breathing and mindfulness exercises) to manage CP-ECD and engage in values-based activities. Older adults have increasingly embraced technologies for health care (known as *digital health*), in part owing to the COVID-19 pandemic [27]. Digital health technologies can enhance the delivery, accessibility (eg, live video), and reinforcement of mind-body interventions (eg, Fitbit [Fitbit Inc] reinforcement of walking goals) to address the CP-ECD comorbidity.

Our interdisciplinary team has iteratively developed the first web-based, mind-body activity program (Active Brains [AB]) aided by a Fitbit to address the CP-ECD comorbidity among older adults [28]. We followed the National Institutes of Health (NIH) Stage Model [29] and used mixed methods to develop and iteratively optimize the program (Figure 1). We conducted and published the following: (1) qualitative focus groups to understand the needs of older patients with CP-ECD and develop AB [28] (NIH stage 1A); (2) a nonrandomized open pilot study with exit interviews to test the feasibility, satisfaction, and preliminary improvements of AB delivered in-person [30] (NIH stage 1A); (3) adaptation of study procedures for fully remote delivery of AB in response to patient preferences and COVID-19 [31] (NIH stage 1A); and (4) a single-blind feasibility randomized clinical trial (RCT) of AB versus an attention-matched education control (Health Enhancement Program [HEP]), both delivered via live video (NIH stage 1B). Results supported the feasibility, acceptability, credibility, satisfaction, and adherence regarding the web-based AB program and study procedures. Signals of improvement were stronger for AB than for the control in multimodal physical function (step count and self-report) and cognitive function (objective cognitive test and self-reported ECD), emotional function (anxiety), pain intensity, and hypothesized mechanistic targets (mindfulness, coping, catastrophic thoughts about pain, and self-efficacy).

**Figure 1 figure1:**
[figure not shown]
Iterative stages of Active Brains intervention development. The study described in this paper was informed by studies 1 to 4 shown in the figure. CD: cognitive decline; CP: chronic pain; R01: 1R01AG075899-01; RCT: randomized clinical trial.

### Objectives

Building on our promising feasibility RCT, we are conducting a web-based RCT of AB versus an attention-matched education control (HEP) in a fully powered study of older adults with CP-ECD (N=260). Randomization is stratified according to ECD type (subjective vs mild cognitive impairment). Our RCT aims to determine the following: (1) efficacy of AB versus HEP on multimodal physical function (coprimary outcomes), cognitive function, emotional function, and pain intensity (secondary outcomes); (2) sustainability of improvements through 6-month follow-up; and (3) mediators (nonadaptive coping, adaptive coping, social factors, and compensatory strategies) and moderators (ECD type, demographics, and clinical variables) of improvement in coprimary and secondary outcomes. To address the lack of diversity in our pilot studies (100% of participants were White) [28,30], our goal is to recruit >38% ethnoracially diverse older adults to align our sample with the US distribution [32]. In this protocol paper, we have described the enhanced methodology, manualized treatments, outcome assessments, current recruitment, and *lessons learned* from the ongoing RCT so far. AB has the potential to be the first evidence-based program for older adults with CP-ECD, with important implications for the prevention of dementia in this high-risk population.

## Methods

### Overview

We are conducting this single-blind, NIH stage-2, fully powered, parallel-group efficacy RCT of the AB intervention versus the HEP control at the Massachusetts General Hospital (MGH). Figure 2 depicts the study flow and procedural timeline. We followed live video and technology guidelines for older adults with CP and ECD from our previous protocol [31].

**Figure 2 figure2:**
[figure not shown]
Study design and timeline. AB-D: Active Brains–digital; HEP: Health Enhancement Program; RA: research assistant; RBANS: Repeatable Battery for the Assessment of Neuropsychological Status.

### Ethical Considerations

The Mass General Brigham institutional review board (IRB) approved all the study procedures (2021P002811).

### Participants

Participants are older adults (aged ≥59 y) with self-reported, nonmalignant, musculoskeletal CP (≥3 mo) and ECD (subjective or mild cognitive impairment). Textbox 1 reports full details about the inclusion and exclusion criteria. These eligibility criteria were informed by similar mind-body trials for CP [33,34] and were refined through our previous AB studies [28,30,31,35]. We included older adults with both ECD types (subjective and mild cognitive impairment) because (1) both types increase the risk for dementia among people with CP [7]; (2) our pilot studies included both ECD types, and we did not observe differences in outcomes or skills use [30,35]; (3) it increases generalizability; and (4) it can help to test moderation by ECD type in this fully powered trial.

Study eligibility criteria and rationale.
**Inclusion criteria and rationale**
Aged ≥59 y—population under studyHave self-identified nonmalignant chronic pain for >3 mo—International Association for the Study of Pain criteria [36]Early cognitive decline (subjective or mild cognitive impairment)—both are comorbid with chronic pain and are precursors to dementiaTelephone Interview for Cognitive Status [37] to confirm the absence of severe cognitive decline that would preclude them from meaningfully engaging with the studyFunctional Activities Questionnaire [38] score <9—to ensure that participants are able to meaningfully engage with the programAble to perform a 6-min walk test at an accelerated pace—the Active Brains intervention will involve increasing the number of steps for the coprimary physical function outcome measureEnglish fluency and literacy—all measures are validated for use in EnglishAbility and willingness to participate and use an ActiGraph watch and smartphone app—the study involves use of multiple technologies, and all participants will receive technological support, but the study requires willingness to learnFree of concurrent psychotropic or pain medication for at least 2 wk before initiation of treatment or stable on current psychotropic or pain medication for a minimum of 6 wk and willing to maintain a stable dose—changing pain or psychotropic medication introduces an additional intervention that may act as a third variable
**Exclusion criteria and rationale**
Diagnosed with dementia or another neurodegenerative disease—these individuals would require a different interventionDiagnosed with a medical illness expected to worsen in the next 6 mo (eg, malignancy)—a serious medical illness may act as a third variableActive, untreated serious mental illness or substance use disorder—participant safetyCurrent, active suicidal ideation—participant safetyStarted a regular mindfulness practice of ≥45 min/wk in the past 6 wk—treatment involves mind-body techniques, and recent initiation of practice would introduce confoundsStarted a course of cognitive behavioral therapy in the last 3 mo—treatment involves cognitive behavioral skills, and recent initiation of treatment would introduce confoundsRegular use of a digital monitoring device to monitor step count—treatment confoundEngage in regular exercise for >30 min/d—treatment confoundNot at risk for falls assessed by the Stopping Elderly Accidents, Deaths, and Injuries Three Key Questions [39,40] or self-reported clearance by a physician for engaging in light physical activity—to ensure the safety of participants

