### Recruitment and Screening

We began recruiting participants in July 2022. Older adults with self-reported ECD and CP are recruited from MGH clinics (Pain Clinic, Memory Unit, Multicultural Alzheimer Prevention Program, and Geriatric Medicine Unit) through multidisciplinary clinician–referred individuals (ie, pain psychologists and geriatricians), by distributing our IRB-approved study flyer through hospital-wide emails via the Rally Research web-based platform, and via social media. Our entirely web-based trial enables us to recruit from the local community and nationally (eg, memory cafes and organizations for older adults). Research assistants log all incoming referred individuals in a REDCap (Research Electronic Data Capture; Vanderbilt University) database (for storing protected health information) and a recruitment log (for tracking the flow of referred individuals and contact attempts). Research assistants conduct individual phone screening to provide study details and determine eligibility. We embedded an R code in the recruitment flyer that allows referred individuals to complete the initial eligibility screening on their own via a simple REDCap checklist. Research assistants answer questions about the study and collect information about availability with all eligible referred individuals. Self-reported CP and ECD are confirmed by referring clinicians and a review of the patient’s medical records when available. Referred individuals that do not meet the study criteria are offered a resource sheet for CP and ECD developed for older patients. The principal investigator confirms all the screening before enrollment and consults with the interdisciplinary team of psychologists, neuropsychologists, and geriatricians as needed.

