#### The 6-Minute Walk Test

After completing RBANS, the clinician instructs the participant to complete the 6-minute walk test outside, on flat terrain using Timed Walk. Timed Walk is a GPS-enabled smartphone app, which enables users to measure walking distance within a fixed time frame. The 6-minute walk test performed using Timed Walk is a valid performance-based measure of physical function and presents a reliable alternative to traditional laboratory assessments [46]. The assessment period is complete once the participants call the research assistant with their 6-minute walk test score.

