#### AB Intervention

##### Overview

The AB intervention is a multimodal walking program informed by the fear-avoidance model [10]. It integrates relaxation response [52], mindfulness [53], pain-specific cognitive behavioral [54], and operant and physical restoration elements [55]. AB teaches skills to break the *disability spiral* of worsening cognitive, physical, emotional, and social functioning in response to comorbid CP and ECD [9,10]. AB skills include the following: (1) *walking skills* to gradually increase step count through individualized quota-based pacing and goal setting reinforced by a digital monitoring device (Fitbit) linked to valued activities; (2) *mind-body skills* to reduce reactivity to pain or cognitive symptoms through diaphragmatic breathing, body scanning, and mindfulness exercises; (3) *pain-cognition*-*behavior* awareness skills to educate on myths about CP and ECD and understand the disability spiral; (4) *cognitive functioning skills* to develop cognitive compensatory strategies and increase intellectual stimulation; and (5) *social-emotional functioning skills* to cope with stress or setbacks and increase social factors (obtaining social support and decreasing isolation) through self-compassion, gratitude, and acceptance (Table 2). The goal is to provide patients with coping skills to manage pain and develop compensatory strategies to improve their physical, cognitive, and emotional function.

**Table 2 table2:** Session outline for the Active Brains (AB) intervention and Health Enhancement Program (HEP) for older adults with chronic pain (CP) and early cognitive decline.

Session	AB topic	AB skills and session content	HEP topic	HEP session content
1	Taking charge of pain and MRP^a^	Deep breathing	Program overview and CP and MRP	Program goals, understanding CP and MRP, how CP and MRP are connected, and the impact of stress
2	Pace yourself	Mindful breathing and quota-based pacing	The connection among CP, MRP, and physical wellness	The connection between CP and MRP
3	Walk all over pain and MRP	Body scan, mindful walking, and gratitude	Sleep and wellness	Healthy sleeping strategies and cognitive and physical health
4	Mindfulness of pain and MRP	Self-compassion and mindful STOP^b^	Exercise and wellness	Physical exercise, maintaining healthy weight, and tips for becoming active
5	Building brain reserve	Mindful focus	Nutrition 1: the basics	Basic nutrition, portion size and calories, and understanding food labels

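### The fall-risk and physician-clearance criterion is listed under Exclusion but worded as a condition for entry, so as written it does not exclude people at fall risk without clearance

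*Protocol article*

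**What the plan says.** The Participants section of the Protocol article refers the reader to the textbox for the criteria: "Textbox 1 reports full details about the inclusion and exclusion criteria". The textbox has an inclusion list and a list headed "Exclusion criteria and rationale". The exclusion list has nine items. The first eight each name something that rules a person out, such as diagnosed dementia, active suicidal ideation or regular daily exercise. The ninth begins with not being at risk for falls on a three-question screen and continues "or self-reported clearance by a physician" "for engaging in light physical activity—to ensure the safety of participants".

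The inclusion list has no item on fall risk or physician clearance. Its nearest entry is being able to do a 6-minute walk test at an accelerated pace.

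Two other places show why the item matters. Participants in both arms do a walking test at each assessment: "the clinician instructs the participant to complete the 6-minute walk test outside, on flat terrain using Timed Walk". The AB arm is then given step goals that rise as they are met: "The AB intervention is a multimodal walking program informed by the fear-avoidance model".

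**The concern.** The item's position and its stated purpose point in opposite directions. Under an exclusion heading, the people described are the ones turned away. Here they are people not at fall risk, or people whose physician has cleared them for light activity. Turning them away does not serve participant safety.

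This is an operative screening rule and the article's only statement on fall risk. It applies to people aged 59 or older with chronic pain and early cognitive decline, who walk fast outdoors with a phone app. The Background section itself lists falls among the adverse events that medication makes more likely. Anyone who uses the article to describe the study population, to replicate the trial or to check a screening form meets a rule that gives the wrong answer if followed.

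**Working it through.** No sample-size, power or error-rate figure is involved, so the check is a truth table on the wording. Inputs, all from the textbox: the list heading (exclusion), the item's two clauses (not at fall risk; cleared by a physician), and the stated rationale (safety).

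The sentence can be parsed in two ways.

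- **Parse 1:** the opening negation governs only the first clause. Excluded if (not at risk) OR (cleared).
- **Parse 2:** the negation governs both clauses. Excluded if NOT (at risk OR cleared), which equals (not at risk) AND (not cleared).

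For comparison, the same sentence read as a condition for entry (with the negation on the first clause) lets a person in if (not at risk) OR (cleared). It therefore excludes only those who are at risk AND not cleared.

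| Fall risk | Clearance | Exclusion, parse 1 | Exclusion, parse 2 | Same sentence as entry condition |
|---|---|---|---|---|
| Not at risk | Cleared | Excluded | Not excluded | Not excluded |
| Not at risk | Not cleared | Excluded | Excluded | Not excluded |
| At risk | Cleared | Excluded | Not excluded | Not excluded |
| At risk | Not cleared | Not excluded | Not excluded | Excluded |

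Comparing each exclusion parse with the entry-condition column:

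- Parse 1 differs in 4 of 4 cells.
- Parse 2 differs in 2 of 4 cells: the two groups without clearance.
- Under both parses the item lets through people at risk without clearance.
- Under both parses it excludes people not at risk who have no clearance. Under parse 1 it also excludes those not at risk who have clearance.

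A reader might supply a missing negative before the second clause, so that lack of clearance becomes a separate ground for exclusion. That would shut out people at risk without clearance, but it needs a word that is not in the text, and it would still exclude everyone not at fall risk.

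Nothing else in the article restates the item or corrects its direction. The inclusion list is silent on fall risk and clearance. The Recruitment and Screening section describes how screening is done, not how this item is scored.

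**The case against.** The strongest reply is that the intended direction is obvious. The item carries its own safety rationale, and no walking trial would mean to turn away people who are not at fall risk. On this view it is a slip in a condensed article that changes no endpoint, analysis or power figure. That stands as an account of how the text probably arose. It does not make the text right: the article says that the textbox gives the criteria in full, and this is its only fall-risk rule.

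Three stronger readings are tempting, and the documents do not support them.

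- **That the 37 participants enrolled by March 2023 entered under this wording.** The article was written after the first year of the trial. Those participants entered under an IRB-approved protocol that is not shown, and nothing says that the textbox wording governed their screening.
- **That the self-screen applied the inverted item literally.** The Recruitment and Screening section says that a code in the flyer "allows referred individuals to complete the initial eligibility screening on their own via a simple REDCap checklist". It does not give the checklist's contents or say that it includes a fall-risk item. The same section describes phone screening by research assistants and confirmation of all screening by the principal investigator before enrolment.
- **That eligibility is reversed for everyone the item covers.** This holds under parse 1 only.

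It is also fair to say that the item does not admit anyone by itself. It fails to exclude, and all the other criteria, including the walking-ability criterion, still apply.

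**Conclusion.** The criterion is wrong as written. Read as an exclusion under either parse, it does not exclude people at fall risk without physician clearance, and it excludes some or all people not at fall risk. Its position therefore conflicts with its stated safety purpose, and no other eligibility item makes up for this.

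The number of people affected cannot be stated. The article gives no prevalence of fall risk or clearance among those screened, and it does not show the screening forms. The finding concerns the text alone. It rests on taking the list heading at its ordinary meaning and on the textbox being the full statement of eligibility, as the article says it is. A reader might infer that unsuitable people were enrolled or suitable ones refused, but there is no evidence of either. The power calculation and the planned analyses are untouched.

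**What to change.** Make the list heading, the item's wording and its safety rationale point the same way, and take the direction from the IRB-approved protocol. Two logically equivalent forms would do this without adding a new clinical threshold: the sentence as worded placed under Inclusion, or its logical negation kept under Exclusion. If it stays under Exclusion, the negation must be written out in full (at risk AND not cleared), so that its scope is not left to the reader.

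Then confirm that the REDCap self-screen and the phone-screen form, where they contain this item, use the reconciled direction. If they do, nothing further is needed. If they do not, check this item in the records of participants already enrolled.

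The cost is a wording correction to the textbox and a short check of two forms, with no effect on design, sample size or power.
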